## Abstract

**Background:**

Lifestyle factors such as physical fitness, dietary habits, mental stress, and sleep quality, are strong predictors of the occurrence, clinical course, and overall treatment outcomes of common cardiovascular diseases. However, these lifestyle factors are rarely monitored, nor used in daily clinical practice and personalized cardiac care. Moreover, non-adherence to long-term self-reporting of these lifestyle factors is common. In the present study, we evaluate adherence to a continuous unobtrusive and patient-friendly lifestyle monitoring system using evidence-based assessment tools.

**Methods:**

In a prospective observational trial (*N* = 100), the project investigates usability of and adherence to a monitoring system for multiple lifestyle factors relevant to cardiovascular disease, i.e., daily physical activity levels, dietary habits, mental stress, smoking, and sleep quality. Patients with coronary artery disease, valvular disease and arrhythmias undergoing an elective intervention are asked to participate. The monitoring system consists of a secured online platform with a custom-built conversational interface—a chatbot—and a wrist-worn wearable medical device. The wrist-worn device collects continuous objective data on physical activity and the chatbot is used to collect self-report data. Participants collect self-reported lifestyle data via the chatbot for a maximum of 4 days every other week; in the same week physiological data are collected for 7 days for 24 h. Data collection starts one week before the intervention and continues until 1-year after discharge. Via a dashboard, patients can observe their lifestyle measures and adherence to self-reporting, set and track personal goals, and share their lifestyle data with practitioners and relatives. The primary outcome of the trial is adherence to using the integrated platform for self-tracking data. The secondary outcomes include system usability, determinants of adherence and the relation between baseline lifestyle behaviour and long-term patient-relevant outcomes.

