## Methods

### Study design

This study is designed as a monocenter prospective observational trial. A total of 100 patients scheduled for, or clinically admitted after a major cardiac intervention will be recruited at Maxima Medical Center in both Eindhoven and Veldhoven. All participants are requested to provide written informed consent before study entry. Demographic and other patient-relevant data are collected at baseline: one week before intervention, or as soon as possible after intervention if it is not possible to include the patient before intervention. Periodic data are collected at baseline, one week, three months, six months, nine months and twelve months after intervention. Continuous lifestyle data are collected 7 days per month for one year after the intervention. The protocol for this study was approved by the Institutional Review Board of Maxima Medical Centre Veldhoven in the Netherlands. The trial is registered at the Netherlands Trial Registry (NTR: NL9861). An overview of the study design is provided in Fig. 1.

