***Objective continuous lifestyle monitoring***			
Daily physical activity	24/7 activity monitoring via health watch (PHB)	Objective	Habitual physical activity 3–5 days of monitoring; sedentary: 5 days of monitoring [16]

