***Subjective continuous lifestyle monitoring***			
Daily dietary habits and drinking behaviour	Self-report via chatbot based on 24 h food diary	Subjective	2–3 days of food records (preferably at least one weekday and one weekend day) [17]
Daily mental stress levels	Self-report via chatbot based on PANAS-scale (as Ecological Momentary Assessment (EMA) [18])	Subjective	No specific frequency, EMA can be adjusted to the design of the study
Daily sleep habits (quantity and quality)	Self-reported via chatbot based on Consensus Sleep Diary [19]; (additionally objectively via health watch)	Subjective (and objective)	At least 7 days including a weekend day [20] (Sleep diary); (5 nights for health watch [21])

The methods were combined in one scheme with a focus on minimizing patient burden and creating regularity. Therefore, the basis of the scheme consists of seven measurement days (based on the minimum habitual sleep measurement frequency, and this includes all days of the week). These seven measurement days are divided over two weeks (for 3 or 4 days per week (2 or 3 weekdays and 1 weekend day)) per four weeks to minimize the activity of the chatbot per week and include measurement free weeks (pause weeks). The first week of reporting contains four reporting days: Monday, Wednesday, Friday and Sunday. The second week of reporting contains three reporting days: Tuesday, Thursday and Saturday. The reporting weeks will take place every other week. Thus, in one month seven days (one complete week of reporting) of measurements is collected. Patients will be asked to wear the health watch in the weeks the chatbot is active to simplify the scheme. The chatbot and health watch scheme can be found in Table 3.

**Table 3 Tab3:** Continuous lifestyle monitoring scheme: “C” = day the chatbot is active. “Wear health watch” = patient is instructed to wear the health watch during the day (night is optional). In the row below the 'Week number' the days of the week are displayed from Monday (M) to Sunday (S)

Week 1							Week 2							Week 3							Week 4						
**M**	**T**	**W**	**T**	**F**	**S**	**S**	**M**	**T**	**W**	**T**	**F**	**S**	**S**	**M**	**T**	**W**	**T**	**F**	**S**	**S**	**M**	**T**	**W**	**T**	**F**	**S**	**S**
**C**		**C**		**C**		**C**									**C**		**C**		**C**								
Wear health watch							Pause							Wear health watch							Pause						

A description of the monitoring method and frequency of each lifestyle domain is described in the following sections.

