##### Daily physical activity level

Daily physical activity will be measured using a health watch (the Philips Health Band (PHB)) [22]. The health watch measures: activity counts, heartrate, respiration rate, total energy expenditure, active energy expenditure, steps, activity type, amount of time the watch has been worn, resting heartrate, recovery heartrate, cardio fitness index and the amount of time a person was asleep or awake.

Patients are asked to wear the health watch for 2 weeks per month (Table 3) for at least 12 h a day, excluding periods for charging the device and periods where the device cannot be worn (such as during washing, showering and swimming).

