##### Daily sleep habits

Daily self-reported sleep quality and quantity is measured via the chatbot based on the Consensus Sleep Diary [19]. 5 items will be asked via the chatbot in the morning when the participant wakes up, with the following outcomes: usual bedtime (time), usual getting up time (time), hours of sleep per night (hours), perceived quality of sleep (Likert-scale), perceived feeling of restfulness (Likert-scale). Secondly, the PHB will objectively measure sleep quantity and quality.

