##### Adherence classification and dropout threshold

Classifications for low, moderate and high adherence are set up to monitor patient’s compliance with providing lifestyle data. The health watch adherence rate, chatbot adherence rate and quarterly assessment completion rates make one-third of the general adherence rate:

$$general\,adherence\,rate\,=\,\left(adherence\,rate\,PHB\,+\,adherence\,rate\,chatbot\,+\,quarterly\,assessment\,completion\,rate\right)/3$$

The chatbot compliance rate is based on the minimum number of days of data collection necessary to gain insight in habitual intake of commonly consumed food. The minimum number of days of data to be collected to gain insight in habitual intake of commonly consumed food is 2–3 days (of food records, real-time monitoring) [17]. Thus, if a patient fills in at least 50% of the measurements, the minimum number of days is certainly met.

The health watch compliance rate is based on the minimum number of days necessary to gain insight in habitual physical activity and sedentary behavior. Previous studies [16] indicate that 3–5 days of monitoring is necessary to assess habitual PA and for sedentary behavior 5-days of monitoring will provide a reliable estimate. Patients were instructed to wear the PHB for at least 12 h a day on average during measurement weeks. Thus, if a patient wears the watch at least 50% of the prescribed time, the minimum number of days certainly is met.

The quarterly lifestyle assessment completion rate is based on the amount of completed quarterly assessments.

The adherence to providing self-tracking data is evaluated by the researchers every four weeks per patient. The total adherence score is a combined score of the chatbot adherence, activity tracker wear adherence and quarterly assessment adherence. The levels are as follows:Low adherence classification: The patient's adherence is below 50% measured over a 4-week interval.Moderate adherence classification: The patient's adherence is between 50 and 75% measured over a 4-week interval.High adherence: The patient’s adherence is above 75% measured over a 4-week interval.

Patients who have a general adherence rate below 50% will be contacted and stimulated to resume using the system by the research nurse once; if patients did not resume after 1 month they are classified as non-adherent.

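### Watch wear is described as round-the-clock in some places and as a 12 h daily minimum in others, and on the 12 h basis the 50% wear rule does not guarantee the five monitoring days claimed for it

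*Protocol article*

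**What the plan says.** Two descriptions of the watch schedule stand in the article.

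- **Round-the-clock.** The abstract (Methods) says that "in the same week physiological data are collected for 7 days for 24 h". Table 2 gives the method for physical activity as "24/7 activity monitoring via health watch (PHB".
- **Daytime minimum.** The section Daily physical activity level says: "Patients are asked to wear the health watch for 2 weeks per month (Table 3) for at least 12 h a day". The caption of Table 3 adds that the "patient is instructed to wear the health watch during the day (night is optional"). The Health watch section repeats the 12 h minimum and leaves wear at night and in pause weeks to the patient.

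The section Adherence classification and dropout threshold restates the instruction as at least 12 h a day, on average, in measurement weeks. It then says that a patient who "wears the watch at least 50% of the prescribed time" is certain to meet the minimum number of days, having cited 3–5 days for habitual activity and 5 days for sedentary behaviour. The watch rate is one third of the general adherence rate. Below 50% is low, 50 to 75% moderate and above 75% high. A general rate below 50% leads to one contact by the research nurse, and a patient who has not resumed after a month is classed as non-adherent.

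On sleep, the section Daily sleep habits says: "Secondly, the PHB will objectively measure sleep quantity and quality". Table 2 lists 5 nights for the watch, in parentheses and as additional to the sleep diary.

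**The concern.** The rule is a share of prescribed time, so it needs a single prescribed time, and the article describes watch data collection in two ways that differ by a factor of two.

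Settling that does not finish the matter. Twelve hours is a floor and is judged on average, while night and pause-week wear are permitted. No stated rule keeps the extra hours out of the numerator. Long wear on a few days can therefore stand in for days not worn at all, and the rate can exceed 100%. Because it is averaged with the chatbot and questionnaire rates, an inflated watch rate can hide non-response in the other two components. What is at stake is the patient's adherence class and whether the nurse contact is triggered.

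A smaller matter is that a patient can follow the wear instruction in full and give no watch-based sleep data.

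**Working it through.** **Inputs.** Measurement weeks: 2 per four weeks, so 14 days (Table 3; Daily physical activity level). Daily wear: 12 h (same section; Health watch; adherence section) or 24 h (abstract). Minimum days: 5 (adherence section). General rate = (watch + chatbot + quarterly)/3. A month is taken as four weeks, as in Tables 2 and 3.

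**1. The plan's own claim, counted in days.** 0.5 × 14 = 7 days, which is at least 5. The claim reproduces if the unit is days.

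**2. The two descriptions in hours per four weeks.**
- Abstract: 14 × 24 = 336 h.
- Wear instruction: 14 × 12 = 168 h.

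A patient who wears the watch 12 h on all 14 days is at 168/336 = 50% or 168/168 = 100%. Assuming for illustration chatbot and quarterly rates of 40% each, the general rate is (50 + 40 + 40)/3 = 43% (low) or (100 + 40 + 40)/3 = 60% (moderate). The adherence section's own wording supports 168 h, which is used below.

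**3. The same claim, counted in hours.** 0.5 × 168 = 84 h.
- At 24 h a day: 84/24 = 3.5 days, below 5.
- Break-even: 84/5 = 16.8 h a day. At any higher average on the days worn, 84 h takes fewer than 5 days' wear.
- In whole calendar days, 84/4 = 21 h a day reaches the threshold in four days.
- Four full days give 96/168 = 57%. With each day capped at 12 h they give 48/168 = 29%.

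**4. Rates above 100%.** Wear of 24 h on all 14 measurement days gives 336/168 = 200%. With no chatbot and no quarterly data:

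| Watch rate | General rate | Class | Nurse contact |
|---|---|---|---|
| 200%, uncapped | 200/3 = 67% | moderate | no |
| 100%, capped | 100/3 = 33% | low | yes |

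Continuous wear is not needed for this. At 18 h a day on 14 days the rate is 252/168 = 150%, and 150/3 = 50%, so the watch alone lifts the patient out of the low class. None of this uses pause-week wear, which would raise the rate further if counted.

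**5. Sleep.** Daytime wear of 12 h on 14 days is 168/168 = 100%, with 0 of the 5 nights listed in Table 2.

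**The case against.** The strongest reply is that the denominator is hardly open. The adherence section gives the 12 h instruction just before it mentions prescribed time, the other wear instructions agree, and the abstract and Table 2 describe data collection rather than what patients are told. This stands. An analyst following the adherence section would use 168 h, so the round-the-clock wording is an inconsistency to correct and not an equally good second denominator.

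A second reply is that caps and counting windows belong in the full protocol or the analysis plan. Their absence alone would be no finding. But the article itself claims that the 50% rule guarantees the minimum days, and with time counted in hours that claim is false on the article's own schedule.

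Third, contact depends on the general rate, an average of three components, and not on the watch rate alone. That is correct, and step 4 is therefore worked on the general rate.

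Three stronger readings are tempting but not supported:

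- A reader might take the statement "Continuous lifestyle data are collected 7 days per month for one year after the intervention" (Study design) as a third wear requirement of 7 × 12 = 84 h, on which 12 h wear on 14 days would score 200%. That sentence does not name the watch. The seven days are the chatbot days, split four and three over two weeks: "Thus, in one month seven days (one complete week of reporting) of measurements is collected". The watch is worn throughout both of those weeks, so the statements are compatible.
- A reader might infer that the primary result changes. The primary outcome is calculated as completers over starters, and neither count is defined by the watch rate.
- A reader might infer that sleep goes unmeasured. Table 2 makes the diary the sleep measure and the watch an addition, and the PSQI is collected periodically.

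**Conclusion.** The point holds in two parts. The abstract and Table 2 do not match the wear instruction and must be reconciled with it; the adherence section points to 168 h per four weeks. On that denominator the 50% rule lacks its stated property when wear is counted in hours: 84 h can come from 3.5 days of continuous wear against a minimum of 5, and the watch rate can reach 200% within the measurement weeks alone. Without a cap, a patient who gives only watch data can score 67% instead of 33% and so miss the contact.

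This rests on prescribed time being counted in hours, on night hours counting towards wear, and on no cap; the article states nothing to the contrary. If the rate counts days, the claim is correct at 7 days. How many patients would be affected depends on how common wear above 16.8 h a day is, which the document does not give. The adherence classes and the contact trigger are affected; the completer-based primary calculation and the sample size are not. The sleep aspect is minor.

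**What to change.** 1. Reconcile the abstract, Table 2, the Table 3 caption, Daily physical activity level, Health watch and the adherence section to one prescribed wear time. Use it as the sole denominator and state whether its unit is hours or days.
2. Count only wear in scheduled measurement weeks and cap each day at the prescribed daily hours. The rate then cannot exceed 100%. With a 12 h cap, 50% needs at least 84/12 = 7 different days. Alternatively, count valid days. The cap alone would still give 50% for 14 days of 6 h (14 × 6 = 84 h); a valid-day count with a stated hourly minimum settles that as well.
3. As a minor addition, report how many four-week windows reach the 5 nights in Table 2 and say that watch-based sleep data depend on voluntary night wear. The diary stays the main sleep measure.

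The cost is wording and a scoring rule. The article lists time worn among the watch's outputs; that daily totals can be extracted is an assumption to confirm. The cap replaces the present averaging, so long days no longer offset short ones and irregular wearers will show somewhat lower rates. No extra burden falls on patients.

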**Discussion:**

Systematic monitoring during daily life is essential to gain insights into patients’ lifestyle behaviour. In this context, adherence to monitoring systems is critical for cardiologists and other care providers to monitor recovery after a cardiac intervention and to detect clinical deterioration. With this project, we will evaluate patients’ adherence to lifestyle monitoring technology. This work contributes to the understanding of patient-centered data collection and interpretation, to enable personalized care after cardiac interventions in order to ultimately improve patient-relevant outcomes and reduce health care costs.

**Trial registration:**

Netherlands Trial Registry (NTR) NL9861. Registered 6th of November 2021.

## Background

Optimization of lifestyle behavior and psychological wellbeing are considered pivotal in cardiac rehabilitation, as physical fitness [1], daily physical activity (PA) levels [2], dietary habits [2], mental stress [2], sleep quality [3, 4], and smoking habits [5] are strongly related to the occurrence, clinical course and overall treatment results of common cardiovascular diseases (CVD’s) such as coronary artery disease (CAD) and cardiac arrhythmias such as atrial fibrillation (AF) [6]. Moreover, quality of life is often not improved after major cardiac interventions [7–9], which may be due to adverse effects of persistent unhealthy lifestyle behaviour on the clinical course of coronary artery disease and atrial fibrillation [9]. However, despite its undisputed relevance, lifestyle behaviour is currently not monitored systematically and therefore not optimally used to the advantage of patients in daily practice [8, 10].

In order to successfully implement lifestyle monitoring in cardiac care pathways, optimizing adherence to self-tracking of lifestyle behaviour via monitoring technologies is essential. Without data provided by the patients, personalized and improved treatment decisions cannot be made. However, there is a gap in literature regarding the adherence to continuous lifestyle monitoring technologies for a longer period of time. Whereas previous research showed high levels of adherence associated with monitoring technology [11, 12], these studies focused on relatively short programs (mostly 1 to 12 weeks). Secondly, studies typically focus on monitoring of one rather than multiple lifestyle domains. Yet, the use of technology to monitor multiple lifestyle domains over a prolonged period of time may be particularly useful as an assistive tool to achieve a healthy lifestyle, and subsequently, better health outcomes in special populations [11]. Therefore, there is a clear need for further research in evaluation of the adherence and usability of this kind of digital health technology in CVD care and management [13].

The Care-On trial evaluates patients’ adherence to monitoring of lifestyle behaviours (i.e. daily physical activity levels, dietary habits, mental stress and sleep quality) with a newly designed system that integrates innovative methods for continuous unobtrusive and patient-friendly in patients with coronary artery disease, valvular disease and arrhythmias. Subsequent system usability, determinants of adherence and the relation between baseline lifestyle behaviour and long-term patient-relevant outcomes are investigated. We postulate that a system that aids patients in monitoring their lifestyle factors will enable better self-management and improve self-motivation [14], with subsequent positive effects on the lifestyle factors themselves and, eventually, on long-term clinical outcomes.

## Methods

### Study design

This study is designed as a monocenter prospective observational trial. A total of 100 patients scheduled for, or clinically admitted after a major cardiac intervention will be recruited at Maxima Medical Center in both Eindhoven and Veldhoven. All participants are requested to provide written informed consent before study entry. Demographic and other patient-relevant data are collected at baseline: one week before intervention, or as soon as possible after intervention if it is not possible to include the patient before intervention. Periodic data are collected at baseline, one week, three months, six months, nine months and twelve months after intervention. Continuous lifestyle data are collected 7 days per month for one year after the intervention. The protocol for this study was approved by the Institutional Review Board of Maxima Medical Centre Veldhoven in the Netherlands. The trial is registered at the Netherlands Trial Registry (NTR: NL9861). An overview of the study design is provided in Fig. 1.

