### Study population

Patients scheduled for or recently having undergone coronary artery bypass surgery (CABG), a fractional flow reserve test (FFR) and/or a percutaneous coronary intervention (PCI), an electrophysiology study (EP) and/or radiofrequency catheter ablation (RFCA), a transcatheter aortic valve implantation (TAVI), and/or valve surgery will be considered for participation. We will include a total of 100 patients. Patients included before their intervention will be monitored one week extra (the week prior to the intervention). A complete list of inclusion and exclusion criteria is provided in Table 1.

**Table 1 Tab1:** Inclusion and exclusion criteria for Care-On

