#### Periodic lifestyle assessment

Patients will be asked to fill in a set of questionnaires (quarterly assessment) at baseline (t0) (one week before intervention), one week after discharge (t1) and at 3 months (t2), 6 month (t3), 9 months (t4) and 12 months after discharge (t5). The results of  the questionnaires related to the patients lifestyle (as described in Table 4) are visualized with a score in the lifestyle monitoring system.

**Table 4 Tab4:** Periodic lifestyle assessment overview

*Periodic lifestyle assessments (quarterly)*		
**Lifestyle parameter**	**Questionnaire**	**Objective**
Perceived physical fitness	FitMáx	The FitMáx [26] used to assess perceived physical fitness as an addition to the daily physical activity data measured by the PHB
Diet quality	NutriMáx (custom FFQ)	A customized healthy diet assessment questionnaire, the NutriMáx (a custom questionnaire based on Dutch Dietary Guideline [23]) is used to assess diet quality and nutrition behavior as an addition to the daily eating habits
Smoking status	Custom questionnaire	The participants will be asked to indicate their smoking status and average amount of smoking (cigarettes per day)
Perceived mental stress	Perceived Stress Scale (PSS-10)	The PSS-10 [27] is used to assess perceived mental stress as an addition to the daily stress level measurements
Perceived sleep quality	Pittsburgh Sleep Quality Index (PSQI)	The PSQI [28] is used to assess perceived sleep quality

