#### Secondary endpoints

The secondary endpoints are:Usability (measured using the SUS, the feedback given by the patients during the phone consults with the research nurse, the quarterly questionnaires and the evaluation interview) and the success rate (percentage of tasks that the patients complete correctly)).Predictors of adherence to the lifestyle monitoring system (demographic and disease characteristics, quality of life, self-efficacy, depressive symptoms and anxiety, motivation, stage of change, fatigue, physical fitness, levels of metal stress, use of a goal tracking functionality, perception of system usability and prior experience with technology. Standardized questionnaires will be used for self-report measures and objective ambulatory measures from the lifestyle monitoring system for objective lifestyle measures).The association between lifestyle behaviour at baseline with clinical outcomes will be examined by evaluating patient clinical records (re-hospitalizations related to cardiac disease) and standardized self-report data (quality of life).

The data will be analyzed using multiple regression analysis. An overview of the questionnaires to be complete by the patients per timepoint for the secondary endpoints is shown in Table 5.

**Table 5 Tab5:** Overview of the assessments of the secondary endpoints of the Care-On study

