		**STUDY PERIOD**						
		Baseline	Rehabilitation					Evaluation
***TIMEPOINT***		***-t1***	***t1***^***2***^	***t2***	***t3***	***t4***	***t5***	***t6***
*Predictors of adherence*								
Health-related Quality of Life	Short Form Health Survey (SF-12) v1 [34]	x	x	x	x	x	x	
Self-efficacy	General Self-Efficacy Scale (GSES) [35]	x						
Depressive symptoms and anxiety	Hospital Anxiety and Depression Scale (HADS) [36]	x						
Motivation and Stage of Change	Readiness-to-Change Lifestyle Questionnaire and Confidence-to-Change Lifestyle Questionnaire [37]	x						
Fatigue	Fatigue Assessment Scale (FAS) [38]	x						
Physical fitness^1^	FitMáx [26]	x	x	x	x	x	x	
Levels of mental stress^1^	PSS-10 [27]	x	x	x	x	x	x	
System usability	SUS [39]	x						x
Mobile Device Proficiency	Mobile Device Proficiency Questionnaire (MDPQ)-16 [40]	x						
*Clinical data*								
Medication adherence	General Adherence Scale (GAS) [41]	x	x	x	x	x	x	
*Usability*								
Satisfaction and usability	Custom questionnaire based on the customer satisfaction score (CSAT) [42] and single ease questions (SEQ) [43]		x	x	x	x	x	
Self-report chatbot and activity tracker usage	Custom questionnaire based on GAS		x	x	x	x	x	

^1^These questionnaires are also part of the periodic lifestyle assessment

^2^The questionnaires of 't1' will not be asked when a patient is included after intervention

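### Baseline is measured before the procedure in some patients and after it in others, and the planned regressions use it as a single variable

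*Protocol article*

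**What the plan says.** All places are in the protocol article.

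- **Study design** recruits by two routes: "A total of 100 patients scheduled for, or clinically admitted after a major cardiac intervention will be recruited". It sets baseline at "one week before intervention, or as soon as possible after intervention if it is not possible to include the patient before intervention".
- **Study population** gives a pre-procedure monitoring week to one route only: "Patients included before their intervention will be monitored one week extra (the week prior to the intervention".
- **Periodic lifestyle assessment** knows only the pre-procedure baseline. The questionnaires are completed "at baseline (t0) (one week before intervention), one week after discharge (t1") and then quarterly.
- **Table 5, footnote 2**: "The questionnaires of 't1' will not be asked when a patient is included after intervention". The first assessment of a patient included late is therefore a post-procedure one, and the next is at three months.
- **Secondary endpoints** names one undivided exposure: "The association between lifestyle behaviour at baseline with clinical outcomes will be examined by evaluating patient clinical records" and self-reported quality of life. The predictors of adherence in the same section include scores that Table 5 schedules at baseline (SF-12, GSES, HADS, FAS, FitMáx, PSS-10).
- **Sample size calculation and statistical analysis** assigns multiple logistic regression to adherence status and re-hospitalization, and linear regression to continuous outcomes such as quality of life. Neither section distinguishes the two kinds of baseline.

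**The concern.** Activity, perceived fitness, fatigue, stress and sleep recorded shortly after a cardiac procedure reflect the procedure as well as the patient's habits. Recorded the week before, they do not. Putting both into one column called baseline adds a shift that depends on when the patient was included.

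Two consequences follow. If inclusion timing is also related to outcome, part of that relation is credited to lifestyle. If timing is unrelated to outcome, the shift acts as measurement error and pulls true associations toward zero. At stake are the secondary aim on baseline lifestyle and later outcomes, and those predictors of adherence that are measured at baseline.

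**Working it through.** **1. The plan's own figure.** The only computed figure is the precision of the one-year adherence proportion: N = 100, 50% expected, interval [0.398, 0.601]. The Clopper-Pearson interval for 50 of 100 is [0.3983, 0.6017], so it reproduces apart from truncation of the upper limit. The simple formula for ±10% gives n = 1.96² × 0.25 / 0.10² = 96.04. Baseline timing enters neither calculation.

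**2. Inputs for the size of the problem.** The documents do not give the share included after the procedure (π), the shift in the measured lifestyle score due to late measurement (d, in within-group SDs), or the relation of timing to outcome. All three are assumptions below.

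**3. Continuous outcome (quality of life).** Let the measured score be X = L − d·T, where L is true lifestyle with variance 1 and T = 1 if included afterwards. Let Y = b·L + g·T + error. The slope of Y on X without a timing term is

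(b − d·g·π(1−π)) / (1 + d²·π(1−π)).

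- *No true effect (b = 0), timing effect g = −0.5:* with π = 0.5 and d = 1, 0.5 × 0.25 / 1.25 = 0.10. With π = 0.1 and d = 0.5, 0.5 × 0.5 × 0.09 / 1.0225 = 0.022.
- *True slope b = 0.30, no timing effect (g = 0), d = 1:* 0.30/1.09 = 0.275 (π = 0.1), 0.30/1.1875 = 0.253 (π = 0.25), 0.30/1.25 = 0.24 (π = 0.5).

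False-positive rate of the lifestyle test at n = 100 (4,000 simulated trials per row, b = 0, g = −0.5):

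| π | d | without timing term | with timing term |
|---|---|---|---|
| 0.1 | 0.5 | 5.2% | 5.2% |
| 0.25 | 1 | 12.1% | 4.7% |
| 0.5 | 1 | 18.8% | 5.4% |

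With g = 0 the rate stays near 5% in either model.

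**4. Binary outcome (re-hospitalization).** Assume no association within either group, 20% re-hospitalized among those included afterwards and 10% among those included before, and π = 0.3 or 0.5. Large-sample logistic simulation gives a pooled odds ratio per SD of about 0.84 to 0.85 for a 1 SD shift and 0.91 to 0.92 for a 0.5 SD shift. With one timing indicator it is about 1.0. At n = 100 the false-positive rate is about 8 to 9% for a 1 SD shift and 5 to 6% for a 0.5 SD shift.

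**5. Events available under the same assumptions.** 100 × (0.3 × 0.20 + 0.7 × 0.10) = 13, or 100 × (0.5 × 0.20 + 0.5 × 0.10) = 15. A timing indicator plus four intervention groups uses 1 + 3 = 4 parameters, or 13/4 = 3.3 to 15/4 = 3.8 events per parameter before any lifestyle variable enters.

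**The case against.** The strongest reply is that the article names model families, not covariate lists, so a timing term may stand in an unseen analysis plan. For adherence, disease characteristics are already listed as predictors and may cover the type of intervention. This is fair: the absence of a timing term is read from silence. But the definition of baseline is not left open. The article fixes it in two incompatible ways and then uses it as a single exposure, and that point stands without any assumption about covariates.

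The second reply is that the bias may be small. This also stands in part. With re-hospitalization as outcome and n = 100, the inflation is at most a few percentage points under the assumptions above, and nothing shows that those assumptions hold.

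Some stronger readings are tempting, and the documents do not support them:

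- *Late inclusions are the more acute patients, or track the type of procedure.* The article says only that earlier inclusion was not possible, and its abstract describes the interventions as elective.
- *One baseline week of sleep diary falls short of the plan's seven-day minimum.* Table 2 states that minimum per four weeks, and the diary is never named as the baseline sleep exposure. The PSQI is scheduled at baseline.
- *t1 could serve as a common post-procedure baseline.* It falls one week after discharge, whereas a late baseline is taken at the first opportunity after the procedure. GSES, HADS and FAS are not collected at t1 at all.

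**Conclusion.** The point holds for the secondary analyses. The article gives two definitions of baseline, and following the broader one mixes pre- and post-procedure measurements in a single regressor. Bias in the associations with re-hospitalization, quality of life and adherence arises if timing is related both to the measured score and to the outcome. Attenuation needs only the first.

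The size cannot be determined from the documents. The pooled null odds ratio of about 0.92 to 0.84 per SD rests on assumed shifts of 0.5 to 1 SD, 20% versus 10% re-hospitalization, and 30 to 50% included afterwards. The direction also depends on the assumed signs. A reader might infer that the secondary aim would report nothing but an artefact of inclusion route. The figures do not go that far. The primary endpoint and the sample size of 100 are untouched.

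**What to change.** 1. Reconcile Study design with Periodic lifestyle assessment, and align the abstract, so that one text says which assessment is baseline for each inclusion route.
2. Record days from intervention to baseline for every patient (negative if before).
3. Include one before/after-intervention indicator in every regression that uses a baseline measure: re-hospitalization, quality of life and adherence.
4. Add the type of intervention only in collapsed form, or where the number of events allows.
5. Report the same models in patients included before intervention as a sensitivity analysis. The indicator removes a shift in the mean. It does not help if the post-procedure score relates to outcome with a different slope, and this subset shows whether that matters.

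No new visits or instruments are needed. The cost is some wording, one date difference per patient, and one degree of freedom. That degree of freedom is not negligible in a re-hospitalization model with perhaps 13 to 15 events, so the number of lifestyle variables entered should be kept correspondingly small. The sensitivity analysis will be imprecise if many patients are included late.
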